#### Sensitivity analyses

2.8.2

We will conduct a sensitivity analysis excluding the final three months of the pre-implementation period to reduce the potential for contamination from NIATx training activities.

#### Power

2.8.3

Power calculations were based on detecting an absolute increase of 5% in PNEP participation, which was considered a realistic and clinically important difference. Estimates were conducted for a fixed sample of nine prisons transitioning over three six-month steps. All model parameters were derived from baseline data from the participating sites (Table 1). Specifically, we incorporated the observed average monthly population of 200 people per prison, a baseline PNEP participation rate of 5%, a within-period intra-cluster correlation coefficient (ICC) of 0.05, and a cluster autocorrelation coefficient (CAC) of 0.95. The correlation structure was modelled with an exponential decay to allow for a different within and between-period ICC. With a two-sided significance level of 0.05, we achieve 95% power to detect a 5% absolute increase (i.e., an increase from 5% to 10%) in PNEP participation. ICC and CAC coefficients were estimated using the ICC Estimation Shiny App [61] and power calculations were performed using the Shiny CRT Calculator [62].

#### Planned subgroup analyses

2.8.4

We will assess whether the effect of NIATx on PNEP uptake differed by prison gender by including interaction terms between gender and the intervention and period effects. This is relevant because while lifetime injection drug use is higher among women than men in Canadian federal prisons [63], baseline uptake of PNEP in women's prisons is lower. This analysis is exploratory and intended to generate a hypothesis regarding gender as a potential effect modifier.

We will also explore the effects of fidelity to NIATx (measured using the fidelity checklist) and staff characteristics (e.g., readiness to change, attitudes towards people who use drugs) on implementation by including these variables as time-varying predictors in the models. This approach will allow us to assess whether improvements in fidelity or changes in staff attitudes over time are associated with increased effectiveness (i.e., higher PNEP participation), as has been observed in previous studies [64,65].

#### Secondary effectiveness outcomes

2.8.5

Secondary outcomes (e.g., PNEP coverage, bloodborne virus testing) will be analyzed using the same approach as the primary outcome. Analyses of secondary outcomes will be considered exploratory given that the trial is powered for the primary outcome.

#### Missing data

2.8.6

We do not anticipate any missing data for the primary or secondary effectiveness outcome measures since they are service-level data extracted by Correctional Service Canada. However, for ethical reasons, counts of ≤5 will be suppressed. We will assume the midpoint (n = 3) where data are suppressed and conduct sensitivity analyses at lower bound (n = 1) and upper bound (n = 5) to assess whether conclusions change.

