	Nova Institution for Women	Nova Scotia	Multi	Women	∼/88 (≤5.7%)	11/86 (12.8%)	9/86 (10.5%)	11/89 (12.4%)	12/93 (12.9%)	17/89 (19.1%)
2	Edmonton Institution for Women	Alberta	Multi	Women	∼/166 (≤3.0%)	∼/169 (≤3.0%)	∼/175 (≤2.9%)	∼/176 (≤2.8%)	∼/177 (≤2.8%)	∼/187 (≤2.7%)
	Grand Valley Institution for Women	Ontario	Multi	Women	∼/220 (≤2.3%)	∼/221 (≤2.3%)	∼/213 (≤2.3%)	∼/228 (≤2.2%)	∼/228 (≤2.2%)	∼/226 (≤2.2%)
	Mission Institution	British Columbia	Medium	Men	14/297 (4.7%)	13/295 (4.4%)	13/289 (4.5%)	13/296 (4.4%)	17/292 (5.8%)	15/294 (5.1%)
3	Fraser Valley Institution for Women	British Columbia	Multi	Women	∼/102 (≤4.9%)	∼/98 (≤5.1%)	∼/104 (≤4.8%)	∼/108 (≤4.6%)	∼/102 (≤4.9%)	∼/104 (≤4.8%)
	Établissement Joliette	Quebec	Multi	Women	∼/103 (≤4.9%)	∼/108 (≤4.6%)	∼/108 (≤4.6%)	∼/106 (≤4.7%)	∼/113 (≤4.4%)	∼/113 (≤4.4%)
	Joyceville Institution	Ontario	Minimum	Men	∼/241 (≤2.1%)	∼/250 (≤2.0%)	∼/260 (≤1.9%)	∼/267 (≤1.9%)	∼/282 (≤1.8%)	∼/278 (≤1.8%)

**Notes.** % of total prison population. ∼ suppressed as count 0≤n ≤ 5; % for these time points are presented as ≤5/total population.

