#### Analysis of the primary outcome

2.8.1

The primary analysis will examine the effect of NIATx on PNEP participation, using a generalised linear mixed model with a negative binomial distribution, comparing the implementation and control periods [41]. The model will include intervention status and time (categorical by month) as fixed effects and a random intercept and period effect (months) at the prison level. Fixed effects represent the group-average structure, with inclusion of time separating the secular trend from the intervention effect [60]. Random effects will account for both within- and between-period intra-cluster correlations. A log offset for prison population size will be included to adjust for differences in prison size and so that results represent the rate of participation, rather than a count of participants. The Kenward-Roger degree-of-freedom correction will be used to account for the small number of clusters. The implementation effect estimate will be expressed as a rate ratio with 95% confidence interval, with the significance level set at α = 0.05.

In a secondary, exploratory non-inferiority analysis of the primary outcome, we will compare the post-implementation (maintenance) period to the late implementation period to examine whether effects are sustained once external facilitation ends. As this is an exploratory analysis and the primary outcome was pre-specified, we will not perform a multiplicity adjustment, with the focus on effect estimates and confidence intervals.

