### Ethics and equity

2.9

The research protocol was approved by the McGill University Health Centre Research Ethics Board (#2023-9201) and the study is registered on ClinicalTrials.gov (Ref NCT07122219). As data are aggregated by prison, individual consent is not required for people in any of the participating prisons. Confidentiality is protected through data aggregation and suppression of small counts. Staff who complete surveys will provide informed consent, and their responses will be kept confidential.

The carceral setting introduces unique ethical and implementation challenges, most notably the tension between security priorities and health care delivery [20]. To safeguard participants, we will monitor for unintended harms, such as increased surveillance or reprisals related to participation. Mitigation strategies will be informed by regular feedback from staff during coaching calls and ongoing engagement with Correctional Service Canada leadership. We will also explicitly address issues of equity. Uptake of PNEP among women remains low in Canadian federal prisons, with some institutions reporting zero participation; this underrepresentation will be monitored in our analyses to ensure equitable access. Collectively, these procedures are intended to ensure that implementation proceeds in a manner that is ethical and equitable, while upholding prison safety and providing insights that are relevant to policymakers and correctional health decisionmakers.

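### Entering every suppressed count as an observed 3 in the primary analysis covers 57% of baseline cells and can pull the rate ratio towards 1; the sensitivity fills of 1 and 5 repair this only in part

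*Protocol article*

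**What the plan says.** The Missing data section states that "for ethical reasons, counts of ≤5 will be suppressed" and continues: "We will assume the midpoint (n = 3) where data are suppressed". The same sentence plans to "conduct sensitivity analyses at lower bound (n = 1) and upper bound (n = 5) to assess whether conclusions change". The constant 3 is therefore the primary-analysis value, and 1 and 5 are sensitivity values.

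The note to Table 1 (Overall design) marks a cell as "suppressed as count 0≤n ≤ 5", and percentages "for these time points are presented as ≤5/total population". Ethics and equity describes low uptake among women, "with some institutions reporting zero participation".

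The primary outcome is analysed "using a generalised linear mixed model with a negative binomial distribution, comparing the implementation and control periods". Month is a categorical fixed effect, prisons have random effects, log population is the offset, and a Kenward-Roger correction is applied. The article relies on "inclusion of time separating the secular trend from the intervention effect".

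**The concern.** Suppression depends on the outcome itself. A prison that moves from 1 participant to 5 is recorded as 3 before and 3 after, so a fivefold rise disappears. Months above 5 enter as observed. The model cannot distinguish a filled 3 from a counted 3, so no uncertainty about the fill reaches the confidence interval.

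The rule reaches far. In Table 1 most baseline cells are suppressed, and five of nine prisons are suppressed in every month. On the six-month activation schedule, sequence 3 is the only sequence still in control in months 13 to 18, and all its baseline cells are suppressed. If its counts stay that low, the month effects in that window rest on constants. The gender subgroup is exposed too, because four of the five women's prisons are suppressed throughout baseline.

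At stake is the size of the primary effect: a true doubling could be reported as clearly less than a doubling.

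**Working it through.** **The plan's own figure.** The Power section gives 95% power for 5% to 10%. A generalised least squares variance reproduces it at 0.950, using 9 prisons, 3 sequences, 4 six-month periods, 200 people per prison-period, ICC 0.05, and decay 0.95 per period. That calculation makes no allowance for suppression.

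**Share suppressed, counted from Table 1.**
- Sequence 1: 1 of 18 (Nova, September 2024).
- Sequence 2: 12 of 18 (Edmonton and Grand Valley, all months).
- Sequence 3: 18 of 18.
- Total: 1 + 12 + 18 = 31, and 31/54 = 57.4%.

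**What the fill does to one prison.** If Y is Poisson with mean m, the expected entered value is F(m) = 3·P(Y ≤ 5) + E[Y; Y > 5]. This gives F(1) = 3.00, F(2) = 3.06, F(3) = 3.30, F(4) = 3.84, F(6) = 5.63 and F(8) = 7.78. A true doubling then appears as:
- 1 to 2: 3.06/3.00 = 1.02
- 2 to 4: 3.84/3.06 = 1.26
- 3 to 6: 5.63/3.30 = 1.70
- 4 to 8: 7.78/3.84 = 2.03

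At low means both conditions become 3 and the prison looks flat: P(Y > 5) at mean 2 is only 1.7%. The loss there is mainly dilution by flat prisons.

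**Whole-trial simulation at the design ratio of 2.** There were 300 runs per scenario with Table 1 populations. Control lasted 6, 12 or 18 months, followed by 24 months of implementation. Counts were Poisson with log-normal monthly noise (SD 0.1). The fitted model was a count mixed model with month effects, intervention, prison intercept, cell-level overdispersion and log-population offset. It approximates the planned model and does not apply Kenward-Roger. The true means in the five fully suppressed prisons are assumptions.

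| Assumed mean | True counts | Fill 3 | Fill 1 | Fill 5 | Coverage, fill 3 |
|---|---|---|---|---|---|
| 1 | 2.00 | 1.48 | 1.72 | 1.39 | 4% |
| 0.5, 1, 2, 3, 4 | 2.01 | 1.75 | 2.27 | 1.52 | 68% |
| 3 | 2.02 | 1.85 | 2.62 | 1.55 | 87% |
| 4 | 2.01 | 2.03 | 2.71 | 1.70 | 98% |

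True counts gave 95% to 97% coverage. A separately coded repeat with mild overdispersion gave 1.50, 1.76, 1.83 and 2.01 for fill 3. A likelihood using only the fact that the count is at most 5 gave 1.99 to 2.04 with 92% to 98% coverage.

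**Other true ratios, fill 3.**
- Ratio 1.5: 1.27 (mean 1), 1.37 (mixed), 1.40 (mean 3), with coverage 55%, 85% and 93%.
- Ratio 1, mixed means, no trend: 1.02, coverage 97%, type I error 3%.
- Ratio 1 with an assumed 2% monthly trend: 0.93 (mean 1) and 0.99 (mixed), coverage 94% and 99%.

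**How far coverage depends on assumed precision.** The stated power implies a standard error on the log-ratio scale of roughly ln 2/(1.96 + 1.645) = 0.192. With d = ln(2/estimate)/0.192, coverage is Φ(1.96 − d) − Φ(−1.96 − d). For 1.48, d = 1.57 and coverage is about 65%. For 1.75, d = 0.69 and coverage is about 89%. For 1.85, d = 0.41 and coverage is about 93%. The biases are the same as in the table, but the coverage losses are much smaller.

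**The bounds.** Table 1 allows 0 in a suppressed cell and the ethics section reports zeros, so the lower bound is 0 and the midpoint is (0 + 5)/2 = 2.5. The Missing data section uses 1 and 3.

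**The case against.** The strongest reply is that the protocol already varies the fill. With a true ratio of 2, at least one of the three planned intervals covered the truth in 99% to 100% of runs in the mixed, mean-3 and mean-4 scenarios. That stands, and the plan deserves credit for it. The cover is incomplete, however: at mean 1 it fell to 76% (93% for a true ratio of 1.5). Each repeat uses one constant in both conditions, so it cannot represent a rise within 0 to 5. With mixed means the estimates ran from 1.52 to 2.27, with nothing to say which is nearer the truth. The stated test is whether conclusions change. At a ratio of 2 all three fills were significant in every run, so that test would pass while the size of the effect stayed unsettled.

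A reader might infer that the rule always biases the ratio, that its intervals generally miss the truth, or that it produces false claims of benefit. The documents do not support this. The true suppressed counts are not shown, bias was absent near a mean of 4 and at a ratio of 1 without a trend, and the usual direction is towards 1. Nor can one coverage figure be defended, since it moves from 4% to about 65% for the same bias as the assumed precision changes.

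It is also fair to say that a censored likelihood does not recover the missing counts. At means 1 and 2, P(Y ≤ 5) is 0.999 and 0.983, so such cells carry almost no information, and the estimate leans on the visible prisons and a common rate ratio.

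**Conclusion.** The concern holds in conditional form. The primary analysis enters a constant as observed data in 31 of 54 baseline cells, including every cell of sequence 3. If the intervention works and true suppressed counts are mostly below about 4, this can attenuate the rate ratio and understate its uncertainty. At the design ratio of 2 the estimate ranges from about 1.5 to about 2.0 over assumed means of 1 to 4. Coverage falls below nominal where there is bias, by an amount that depends on the assumed correlation. The reported zeros make the low-count scenarios plausible but do not establish them.

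Separately, and with no assumption needed, the lower bound of 1 contradicts Table 1 and the ethics section. The sensitivity analyses do not span the range that was suppressed.

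**What to change.** In the primary analysis, treat each suppressed cell as interval-censored on 0 to 5 within the planned count mixed model, so that it contributes P(Y ≤ 5). Alternatively, multiply impute suppressed cells from the model's distribution truncated to 0 to 5. With the second route each completed data set can be fitted with the planned model and small-sample correction.

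Keep the constant fills as sensitivity analyses, with the lower bound corrected to 0, and make the Missing data section agree with the Table 1 note.

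The cost is revised analysis wording and some extra programming, with no new data. Intervals will be wider, and the result will rely more on the visible prisons and on a common rate ratio; the report should say so. The change should be made before the outcome analysis.

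### The suppressed-count sensitivity values of 1 and 5 do not bound the effect: suppressed cells can be 0, and one common fill cannot span a ratio between periods

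*Protocol article*

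**What the plan says.** Three places in the protocol article bear on this.

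- **Section 2.8.6 (Missing data).** The rule is that "counts of ≤5 will be suppressed", with no exemption for zero. The main analysis uses a single value: "We will assume the midpoint (n = 3) where data are suppressed". The plan will then "conduct sensitivity analyses at lower bound (n = 1) and upper bound (n = 5") to see whether the conclusions hold. No scenario lets the fill differ between control and implementation months.
- **Table 1 note (section 2.3).** A masked cell is described as "suppressed as count 0≤n ≤ 5", and percentages "for these time points are presented as ≤5/total population".
- **Section 2.8.1 (primary analysis).** The result is a ratio between conditions: "The implementation effect estimate will be expressed as a rate ratio with 95% confidence interval". The model is a negative binomial mixed model with a log population offset, and "The model will include intervention status and time (categorical by month) as fixed effects".

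Section 2.9 adds, on women's uptake, "with some institutions reporting zero participation".

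**The concern.** There are two separate problems.

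1. **The range is inconsistent.** By the Table 1 note a hidden count can be 0. A sensitivity run at 1 is then not a run at the lower bound, and it leaves out the part of the range where a ratio with a small denominator moves most.
2. **A common fill tests the wrong thing.** Raising or lowering all hidden counts together mainly changes the assumed level of uptake. The primary estimate is a change between conditions. Its extremes arise when hidden control counts are low and hidden implementation counts high, or the reverse, and no planned run covers either case.

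What is at stake is the robustness statement that will accompany the primary result. Runs at 1, 3 and 5 could agree closely although the hidden data are compatible with a much wider set of rate ratios.

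**Working it through.** **1. The plan's own midpoint.** (1 + 5)/2 = 3 reproduces the stated value. With the Table 1 range, (0 + 5)/2 = 2.5. The stated figures therefore assume a range of 1 to 5.

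**2. How much of the baseline is hidden (counted from Table 1).** Group 1 has 1 of 18 prison-months suppressed, group 2 has 12 of 18 and group 3 has 18 of 18: 31 of 54 in total. Five prisons (two in group 2, three in group 3) are suppressed in all six months.

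**3. Effect on baseline level.** The visible counts sum to 100 + 72 + 60 + 85 = 317, over 11,094 person-months. The pooled rate is (317 + 31 × fill)/11,094. Group 3 has 618 + 651 + 1,578 = 2,847 person-months, so its rate is 18 × fill/2,847.

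| Fill | Pooled baseline | Group 3 baseline |
|---|---|---|
| 0 | 2.86% | 0% |
| 1 | 3.14% | 0.63% |
| 2.5 | 3.56% | 1.58% |
| 3 | 3.70% | 1.90% |
| 5 | 4.25% | 3.16% |

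**4. One prison suppressed in both conditions.** The crude count ratio under a common fill f is f/f = 1, whatever f is. With counts from 1 to 5 the attainable ratio runs from 1/5 = 0.2 to 5/1 = 5. With 0 allowed it runs from 0 upwards without limit.

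**5. Illustrative model.** This is a Poisson log-linear model with prison and month fixed effects and a log population offset, over 24 months with steps at months 6, 12 and 18. It is simpler than the planned negative binomial mixed model. Populations are close to the Table 1 averages. The four largely visible prisons start at 7.2%, 3.3%, 12% and 4.8%. The other five are taken as suppressed throughout, which is an assumption because the article gives baseline counts only. Zero is entered as a very small positive number.

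| Fill (control / implementation) | Visible prisons RR 1.0 | Visible prisons RR 1.5 |
|---|---|---|
| 1 / 1 | 1.00 | 1.40 |
| 3 / 3 | 1.00 | 1.31 |
| 5 / 5 | 1.00 | 1.26 |
| 5 / 1 | 0.68 | 0.90 |
| 1 / 5 | 1.77 | 2.27 |
| 5 / 0 | 0.60 | 0.82 |
| 0 / 5 | 2.48 | 3.18 |

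With no effect in the visible prisons, the planned runs span a range of zero width. Condition-specific fills on 0 to 5 span 0.60 to 2.48.

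**6. A case in which the planned runs all miss on the same side.** Let uptake double everywhere, with the hidden prisons going from 1 to 2 per month. The true rate ratio in this model is 2.00. Common fills of 1, 3 and 5 give 1.77, 1.58 and 1.49.

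**7. Suppression in control months only.** Let the five prisons be hidden in control and show 8 in implementation, with RR 1.5 in the visible prisons. Common fills of 5, 3, 1 and 0 give 1.55, 1.97, 2.97 and about 4.29. Stopping at 1 leaves out the stretch from 2.97 to about 4.29.

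**The case against.** **Hidden counts in both conditions are assumed.** At the 10% uptake used for power, even the smallest population in Table 1 (86) gives 8.6 participants, so suppression would fall mainly in control months. In that case common fills of 0 and 5 would bracket a prison's ratio. This stands as a limit on the second problem, which arises only if small prisons stay at 5 or fewer after activation. That is plausible, since five prisons are there throughout baseline, but it is not established. The argument does not rescue a lower value of 1 (step 7).

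**Opposed fills are extreme.** Filling 5 in every hidden control month and 0 in every hidden implementation month gives RR 1.01 in the illustrative model even when visible uptake doubles, and 1.37 when it triples. A rule that calls the result robust only if it survives both opposed fills would be close to impossible to pass. This stands: such runs belong in the report as extremes, not as a criterion.

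**A fill of 2.5 is not a count.** The planned model is for counts, and moving from 3 to 2.5 changes pooled baseline uptake only from 3.70% to 3.56%. This also stands. The integer 3 is usable as a working value.

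**The remark on zero participation is weak support.** Section 2.9 gives no dates or prisons, and the zeros may be known to the team. The Table 1 note carries the point alone.

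A reader might infer that the planned fills would manufacture a benefit. The documents do not support that. In step 6 every common fill errs towards no effect, and the direction in the trial depends on counts not yet available.

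**Conclusion.** The point holds on both parts, in a limited form. By the article's own definition of a suppressed cell, 1 is not the lower bound and 3 is not the midpoint. Runs with one common value cannot bound the rate ratio when a prison is suppressed in both conditions, so their agreement is not evidence of robustness. The share of data affected is large: 31 of 54 baseline prison-months and five of nine prisons throughout.

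The range of 0.60 to 2.48 against a constant 1.00 rests on assumed implementation-period counts and a simplified Poisson model. It shows the direction and possible size of the gap, not the trial's result. Five is a correct upper bound for a single cell. Nothing here shows that the primary estimate will be wrong, or that a result must survive the most extreme fills to be credible.

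**What to change.** - In section 2.8.6, set the lower sensitivity value to 0 so that it agrees with the Table 1 note. The value 3 may stay as a working fill if it is no longer called the midpoint of the range.
- Add supplementary analyses in which the fill differs by condition (control low with implementation high, and the reverse), labelled as extreme scenarios and not used as a pass/fail rule. Alternatively, fit a likelihood that treats suppressed cells as interval-censored on 0 to 5.
- Describe the common-fill runs as a check on the assumed level of uptake, not as bounds on the effect.

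The cost is one changed number, some rewording and a few extra model runs. The reported sensitivity range will be wider. Trial conduct and data collection do not change.

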### Ethics and equity

2.9

The research protocol was approved by the McGill University Health Centre Research Ethics Board (#2023-9201) and the study is registered on ClinicalTrials.gov (Ref NCT07122219). As data are aggregated by prison, individual consent is not required for people in any of the participating prisons. Confidentiality is protected through data aggregation and suppression of small counts. Staff who complete surveys will provide informed consent, and their responses will be kept confidential.

The carceral setting introduces unique ethical and implementation challenges, most notably the tension between security priorities and health care delivery [20]. To safeguard participants, we will monitor for unintended harms, such as increased surveillance or reprisals related to participation. Mitigation strategies will be informed by regular feedback from staff during coaching calls and ongoing engagement with Correctional Service Canada leadership. We will also explicitly address issues of equity. Uptake of PNEP among women remains low in Canadian federal prisons, with some institutions reporting zero participation; this underrepresentation will be monitored in our analyses to ensure equitable access. Collectively, these procedures are intended to ensure that implementation proceeds in a manner that is ethical and equitable, while upholding prison safety and providing insights that are relevant to policymakers and correctional health decisionmakers.

